### Randomization and blinding

The block randomization sequence will be computer-generated and implemented by a person who will not participate in recruitment, evaluation, or treatment. The randomization sequence will be masked using opaque envelopes sealed and sequentially numbered. Each envelope will correspond to one of the two study groups and will be opened after the initial assessments through a video call. The nature of the intervention will not allow the blinding of the physiotherapist who will provide the behavioral intervention. However, the outcome assessors will be blinded to the allocation of patients into groups and patients will be masked to each treatment they are receiving.

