### Design and setting

This double-blind (trial participants and outcome assessors) multicenter randomized clinical trial is expected to be carried out between February 2022 and November 2023. Patients will be contacted by a researcher involved in this study, informed about the study, and invited to participate. If they agree to participate, the inclusion criteria will be applied. All patients will be assessed before and immediately after the intervention (i.e., after the 12 weeks of intervention commencement), as well as 6 months after that (Fig. 1). Patients who discontinue the intervention protocol will be invited to a follow-up assessment. Research assessments will be carried out in person by trained assessors in both centers (Londrina and São Paulo), and the interventions will be carried out online by the main investigator from the coordinating center (Londrina).

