**Fig. 1 Fig1:**
[figure not shown]
SPIRIT schedule of study enrolment, interventions, and assessments (*−t1=* enrolment; *0*= allocation; *t*_*1*_= post intervention; *t*_*2*_= 6 months after the end of intervention)

After the initial assessment, patients will be randomized into 2 groups: control group (CG) or intervention group (IG). Both groups will receive a minimal intervention (educational program), which will be explained further. The IG will receive weekly individual online sessions and also some online group sessions for 12 weeks of motivation-based BC intervention to promote PA and reduce sedentary behavior. The intervention group will also receive an activity monitor with instructions on how to use. Patients will be instructed to maintain their controller asthma medications during the intervention; however, if it is needed to change, they should record it in the asthma symptoms and medication control diary (explanation further). The study flowchart is shown in Fig. 2.

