### Interventions

#### Educational program

The educational program will be delivered similarly to both groups through videos, images, and a booklet. After the initial assessment, all participants will receive a quick welcome video call, in which they will be randomized (see details further) and informed on how this program will work. After that, the educational videos and booklet will be sent daily for 5 subsequent days. Later, one educational image will be sent every other week up to the 12 weeks completion. Participants will be able to ask questions any time, if they want to. The program will cover information regarding the respiratory system, asthma pathophysiology and treatment, prevention strategies, and medication instructions [15]. It will also be briefly addressed the subjects: understanding PA and sedentarism, as well as the importance and benefits of being physically active and less sedentary [17].

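### The trial is described as double-blind with masked participants, but only one arm receives coaching, a step counter and goals, so at most it is assessor-blinded

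*Protocol article*

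**What the plan says.** Three places in the protocol article claim masking of participants. The Methods paragraph of the Abstract labels the trial double-blind. Design and setting says who is meant: "This double-blind (trial participants and outcome assessors) multicenter randomized clinical trial". Randomization and blinding ends with the statement that "patients will be masked to each treatment they are receiving".

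The same section treats the other parties separately. For the provider it concedes: "The nature of the intervention will not allow the blinding of the physiotherapist". For the assessors it says that "the outcome assessors will be blinded to the allocation of patients into groups".

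The arms are described as follows. On the shared component: "The educational program will be delivered similarly to both groups through videos, images, and a booklet". On what is added in one arm only: "The IG will receive weekly individual online sessions and also some online group sessions for 12 weeks", and "The intervention group will also receive an activity monitor with instructions on how to use". On the timing of allocation, after the initial assessment "all participants will receive a quick welcome video call, in which they will be randomized".

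**The concern.** A participant is masked to treatment only if the experience of one arm cannot be told from the experience of the other, usually because a sham or matched contact stands in for the active component. Nothing of that kind appears here. The label double-blind therefore claims a property that the described design does not have.

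The label matters because many of the secondary outcomes are the participant's own ratings. A person who knows that they are being coached each week may rate symptoms, mood or motivation more favourably because they expect to improve or want to please the therapist. Blinding the person who hands over the questionnaire does not remove that. A reader who takes the label at face value would give these results more protection than they have.

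**Working it through.** The point involves no figure, so the check sets the sections side by side.

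**Step 1: what each arm experiences.**

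| Component | Control | Intervention | Section |
|---|---|---|---|
| Videos and booklet over five days, then an image every two weeks to week 12 | yes | yes | Educational program |
| 12 weekly video sessions of about 30 minutes, four of them in a group | no | yes | Behavior change intervention |
| Fitbit Zip with a step display, values written in a diary each day | no | yes | Behavior change intervention |
| Weekly step goal, raised by 6 to 10% when the patient feels ready | no | yes | Behavior change intervention |
| Commitment contract, group challenges, games with other participants | no | yes | Behavior change intervention and Table 1 |
| Sham monitor or attention-matched contact | none described | not applicable | – |

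**Step 2: can the recipient be unaware of this?** No. Every item that differs between the arms is something the participant does, wears or attends. The article accepts that the nature of the intervention unblinds the physiotherapist. The participant is on the other side of the same sessions, so the same reasoning applies.

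**Step 3: what masking could still exist.** Both arms receive a programme that touches on physical activity. A control participant might therefore not know that a coaching arm exists, and participants in either arm might not know the hypothesis. That is masking to the hypothesis or to the other arm's content. The sentence in Randomization and blinding claims something different, namely masking to the treatment being received.

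**Step 4: which outcomes depend on participant masking.**

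- *Participant-reported:* ACQ-6, AQLQ, Pittsburgh Sleep Quality Index, Epworth Sleepiness Scale, Hospital Anxiety and Depression Scale, the Basic Psychological Needs in Exercise Scale and BREQ-3. That is seven questionnaires. The symptom, exacerbation and medication diary makes eight instruments.
- *Effort-dependent but assessor-measured:* step test, sit-to-stand, Timed Up-and-Go, 4-metre gait speed and spirometry. Participant effort can still respond to knowledge of treatment, but the planned assessor blinding keeps its value.
- *Device-measured:* the Actigraph primary outcomes and Actiwatch sleep variables. Reporting bias does not act on these directly, although an unmasked participant can still behave differently during the 7 days of wear.

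**Step 5: map to the stated aims.** Secondary aim I has five domains. Asthma control, quality of life, and anxiety and depression rest on self-report (three of five). Sleep quality rests on it in part, with the Actiwatch alongside. Functional capacity does not rest on it. Secondary aim II (needs satisfaction, self-determination, autonomous motivation) rests on self-report entirely, and Table 1 shows sessions built around the same three needs that participants then rate. The Statistical analysis section also plans a between-group comparison of ACQ and AQLQ responders at 0.5 points, and correlations of activity change with asthma control or quality of life.

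**The case against.** The best defence is that the sentence is loosely worded and means masking to group identity. The welcome call is described as covering randomisation and how the programme works; the article does not say that the other arm's content is disclosed. The consent text is not part of what is shown, so what participants are told cannot be checked. This part stands: partial masking of that kind may exist, and the correction should leave room for it. It does not rescue the sentence, which refers to the treatment received.

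A second defence is that the arm differences are openly described, so a careful reader can judge the masking unaided, and that the primary outcomes, the sample size and the primary analysis do not depend on participant masking. This is also correct and limits the seriousness. It does not make the label true.

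A reader might infer more than the documents support:

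- *That only the accelerometer and Actiwatch results have any protection.* The timed and counted tests and spirometry are partly protected by blinded assessors.
- *That expectation alone could produce a 0.5-point change on ACQ or AQLQ.* The article gives no figure from which such an effect could be sized.
- *That the self-reported outcomes can support only exploratory claims.* Unmasked patient-reported outcomes are not invalid, and they are already secondary here; downgrading them further is a matter of preference.
- *That the title and registry entry are also wrong.* Neither the title nor the registry's masking field can be seen in the material reviewed.

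**Conclusion.** The point holds as an error of description. The Abstract, Design and setting, and Randomization and blinding sections attribute to the trial a participant masking that its own intervention sections exclude. On the text shown, the trial is assessor-blinded.

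The consequence is moderate. Eight participant-reported instruments, covering all of secondary aim II and most of aim I, are unmasked and need to be read with that risk of bias. The direction and size of any bias cannot be stated from the article. The primary conclusion on activity and sedentary behaviour is little affected, because it rests on accelerometer data.

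This assumes that no sham monitor or matched contact exists beyond what is described, and that assessor blinding is carried out as planned.

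**What to change.** 1. In the Abstract and in Design and setting, replace double-blind with assessor-blinded and drop participants from the list of blinded parties.
2. In Randomization and blinding, replace the clause on patients with wording such as: *Patients are not masked to the treatment they receive.* If it is true, add: *They are not told the study hypothesis or the content of the other arm.*
3. In Outcome measures or Statistical analysis, state that ACQ-6, AQLQ, the Pittsburgh and Epworth scales, the Hospital Anxiety and Depression Scale, the psychological needs scale, BREQ-3 and the symptom and exacerbation diary are reported by unmasked participants and will be interpreted with that risk of bias. Note there that the performance tests depend on effort but keep assessor blinding, and that the accelerometer outcomes are not directly exposed to reporting bias.

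The Ethics section already commits to reporting protocol changes in the results article, so the correction has a place to be recorded. The cost is wording only, with no change to conduct, sample size or analysis. The drawback is that the stated blinding becomes less favourable.

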### Statistical analysis

Statistical analysis will be performed after post-intervention and follow-up assessments using the software SPSS Statistics V22.0 (IBM, USA). Data distribution will be analyzed using the Shapiro-Wilk test. Variables will be presented as mean (SD), median [interquartile range 25–75%] according to data distribution. Categorical variables will be presented as absolute and relative frequency. The magnitude of statistical estimates will be presented using 95% CI. The results will be analyzed according to the intention-to-treat principle, as recommended by the CONSORT statement [40]. Per-protocol analysis might be performed to contrast results. Mixed model ANOVA will be used to identify the effect of the protocol to promote physical activity and reduce sedentary behavior. The repeated measures factor will be “time” (pre- and post-intervention evaluation) and the independent measures factor will be the “group” (control group or intervention group). To compare the proportion of patients that achieved the minimal clinical important difference in ACQ and AQLQ (0.5 points for both) [22, 41] between groups, the chi-square test will be used. Pearson or Spearman correlation coefficients will be used to verify the relationship between the changes in PA and changes in asthma control or quality of life. Values of *P* <0.05 will be considered statistically significant.

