### Sample size calculation

The sample calculation was based on a previous study with adults with asthma in which two groups performed a 12-week intervention to increase physical activity, and the number of steps/day obtained in both groups (control and experimental) were normally distributed with the following values after the intervention: 6248±2030 and 8853±3320 steps/day, respectively [11]. Therefore, for the present study, a total sample of 38 people will be needed to reject the null hypothesis, with a power of 0.8 and a value of *P*<0.05. However, considering a 20% drop-out rate [13] throughout the study, the final sample size will be 46 people (23 in each group).

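### Intention-to-treat is promised, but the pre/post mixed ANOVA in its classical form leaves out participants without a 12-week value and can be biased if loss depends on baseline activity

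*Protocol article*

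**What the plan says.** The Statistical analysis section of the protocol article sets the principle: "The results will be analyzed according to the intention-to-treat principle, as recommended by the CONSORT statement". It then fixes the primary model: "Mixed model ANOVA will be used to identify the effect of the protocol to promote physical activity and reduce sedentary behavior". The factors are given as "The repeated measures factor will be “time” (pre- and post-intervention evaluation) and the independent measures factor will be the “group” (control group or intervention group"). The same section keeps a further option open: "Per-protocol analysis might be performed to contrast results". The software is SPSS, with no procedure named.

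Two other sections bear on this. Sample size calculation arrives at 38 participants for the test and raises this to 46, "considering a 20% drop-out rate [13] throughout the study". Design and setting says: "Patients who discontinue the intervention protocol will be invited to a follow-up assessment".

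The article gives no rule for participants who lack a 12-week accelerometer value, and it does not define the analysed set.

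**The concern.** A repeated-measures factor with two levels crossed with a between-subject factor is the usual description of a split-plot ANOVA. With two time points, its group-by-time test is the t-test on individual change. A participant with no post value has no change and drops out of the test. The principle stated in the section and the model named in it then pull apart.

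The sample size section fits this reading, because enlarging 38 to 46 treats drop-outs as lost to the test. Two further consequences follow:

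- A participant with baseline and 6-month data but no 12-week value contributes nothing to the pre/post test, although discontinuers are invited back for assessment.
- The optional per-protocol analysis loses much of its contrast if the main analysis has already lost everyone without a post value.

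Bias is the main stake. Weekly motivational sessions are compared with a low-contact educational programme, so the two arms may well lose different kinds of participant. Where loss depends on baseline activity, the completers in the two arms no longer share a baseline distribution. A comparison of change scores does not correct for that.

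**Working it through.** **Inputs from the Sample size calculation section.** Post-intervention steps/day are 6248 (SD 2030) in control and 8853 (SD 3320) in the experimental arm. Power is 0.80 and the significance level 0.05. N is 38, then 46 (23 per arm), with 20% drop-out over the whole study.

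**1. The plan's own figures**
- Difference: 8853 − 6248 = 2605. Pooled SD: √((2030² + 3320²)/2) = 2752. Standardised effect: 2605/2752 = 0.947.
- A two-sided t-test needs 19 per arm, 38 in total, with power 0.810. This matches the plan.
- Inflation: 38 × 1.2 = 45.6, rounded to 46. This also matches.

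**2. How many could be left out, and the effect on power**
- Upper value at 12 weeks: 0.20 × 46 = 9.2, so about 9, leaving 36.8.
- Power of the same t-test is 0.788 with 18 + 18 analysed, 0.799 with 18 + 19, and 0.881 with all 46.
- Loss of power relative to the 0.80 target is therefore negligible.

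**3. Bias of the change-score estimate when loss depends on baseline**

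Assumptions that are not in the documents:
- SD 2750 at both visits (the pooled SD rounded) and normal baseline values.
- A true effect of 2605.
- Pre/post correlation ρ from 0.3 to 0.8.
- In the intervention arm, 40% loss below the baseline mean and none above it, so 20% loss in that arm. In the control arm, 20% loss at random.

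Steps:
- Share of intervention-arm completers below the mean: 0.5 × 0.6/0.8 = 0.375. Share above: 0.5/0.8 = 0.625.
- The mean of each half lies 0.798 SD from the centre. Completers' baseline shift: (0.625 − 0.375) × 0.798 × 2750 ≈ 549 steps.
- The expected post value shifts by ρ × 549, so the expected change shifts by −(1 − ρ) × 549.

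| ρ | Bias, one arm selected | % of 2605 | Bias, both arms with opposite selection | % of 2605 |
|---|---|---|---|---|
| 0.3 | −384 | −15% | −769 | −30% |
| 0.5 | −274 | −11% | −549 | −21% |
| 0.7 | −165 | −6% | −329 | −13% |
| 0.8 | −110 | −4% | −220 | −8% |

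Simulation of the same scenarios (8,000 trials per setting) gave mean change-score estimates of 2224, 2322, 2445 and 2499 with one arm selected, and 1836, 2067, 2273 and 2396 with both. A baseline-adjusted analysis stayed within about 12 steps of 2605.

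A milder, graded dependence on baseline (loss of 18% to 19%, only 200 runs) gave 2438 for change scores and 2626 for a linear mixed model at ρ = 0.5, with a Monte Carlo standard error of about 64 for the former. At ρ = 0.7 the estimates were 2554 and 2689, neither clearly off the true value.

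**4. Loss that depends on the unseen outcome**

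If the 20% lost from the intervention arm would have gained nothing over control, the effect in all randomised participants is 0.8 × 2605 = 2084. Completers still show about 2605, which is 2605/2084 = 1.25 times as much. A mixed model that assumes missing at random would also give about 2605.

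**The case against.** The strongest reply is that the article never says anyone is excluded. The model name is loose: it could mean a linear mixed model, which the same software fits and which keeps participants with only a baseline value. Imputation before an ANOVA is not ruled out either. Missing-data rules are commonly left to a full protocol or analysis plan not shown here, and analysing people in their assigned arm is compatible with an ANOVA.

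Much of this stands. A reader might infer that the primary result will certainly be a complete-case analysis with a fifth of the sample removed. The documents do not support that, for two reasons. Exclusion is an inference from the factor description. And the 20% covers the whole study, including the visit 6 months after the intervention, while those who stop the intervention are invited to be assessed. About 9 of 46 is therefore an upper planning value at 12 weeks.

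Two stronger size claims also fail:
- A bias of −21% does not come from selection in one arm. It needs opposite selection in both arms at once, at an assumed correlation of 0.5.
- The 25% overstatement in step 4 is not a consequence of choosing ANOVA, since a mixed model would show it too.

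The drop-out patterns are illustrative, and those shown pull the estimate towards no effect. By symmetry, the reverse selection would push it the other way by the same amount.

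What the reply does not remove is that the article names a model and describes its factors, and that model as described does not deliver the stated principle. This goes beyond a detail left for later.

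**Conclusion.** The point holds in a limited form. Read in the classical way that its factor description suggests, the primary model excludes participants without a 12-week value, and nothing shown reconciles this with intention-to-treat. The number affected is at most about 9 of 46 on the plan's own drop-out allowance, and it may well be smaller.

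The consequence is possible bias and a misleading label, with little effect on power. The illustrated size is about −15% to −4% of the assumed effect when loss in one arm depends on baseline, and about double with opposite selection in the other arm. These figures rest on the assumed correlation, SD and drop-out pattern. If loss is unrelated to baseline and outcome, or similar in both arms, the bias largely disappears. The change is worth making because it is cheap and removes the part of the bias that depends on observed baseline.

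**What to change.** In the Statistical analysis section:

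- Replace the mixed ANOVA with a likelihood-based linear mixed model (SPSS MIXED). It should analyse every randomised participant with any accelerometer value, in the arm assigned. Baseline should be part of the outcome vector, with means set equal across arms. Because the initial assessment precedes randomisation, this should keep nearly all 46 participants.
- Define the analysed set in those terms. If a paired pre/post ANOVA is reported as well, label it complete-case.
- Add one sensitivity analysis for missing-not-at-random loss, for example giving intervention-arm drop-outs no gain over control. The mixed model alone does not address that kind of loss.

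If a likelihood-based model was intended all along, the first two items need only a clarifying sentence. The cost is a little extra analysis work, with no new data, software or participants.

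### The sample size is derived for post-intervention steps/day, but the planned time-by-group ANOVA tests change without baseline adjustment, so the stated 0.8 power is not established for that analysis

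*Protocol article*

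**What the plan says.** Under Sample size calculation, the protocol article takes steps/day from an earlier 12-week trial in adults with asthma. The control and experimental values are described as "normally distributed with the following values after the intervention: 6248±2030 and 8853±3320 steps/day, respectively". From these it concludes that "a total sample of 38 people will be needed to reject the null hypothesis, with a power of 0.8". The total is raised to 46 (23 per group) for 20% drop-out. No baseline value, SD of change or pre-post correlation appears.

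Under Statistical analysis, the method for the primary outcomes is: "Mixed model ANOVA will be used to identify the effect of the protocol to promote physical activity and reduce sedentary behavior". The repeated factor is time, with a pre- and a post-intervention level, and the between-subject factor is group. Baseline therefore enters as one level of the outcome. No baseline covariate is named, and the article does not say which term of the model is the test. P values "<0.05 will be considered statistically significant".

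**The concern.** The two sections describe different tests. The sample size rests on comparing two groups after the intervention. A model with time (two levels) and group has three terms:

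- The time effect averages over the groups.
- The group effect averages over pre and post, so half of it is a baseline difference that randomisation makes zero in expectation.
- The group-by-time interaction compares change between groups, and is the only term that isolates the treatment effect.

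The interaction has its own variance, which depends on how strongly baseline and post-intervention steps correlate. A power figure worked out for post-intervention values carries over only at one particular correlation. The sample size section is the article's only support for the trial's size, and as written it does not cover the planned test. The baseline accelerometer week is already collected and could be used more efficiently.

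**Working it through.** **Inputs from the article.** Control 6248 ± 2030 and experimental 8853 ± 3320 steps/day after the intervention; power 0.8; alpha 0.05; 38 evaluable; 46 enrolled; 20% drop-out. Sidedness is not stated.

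**Assumed inputs.** Pre-post correlation rho, shown over a range. Baseline SD equal to the pooled post-intervention SD, varied in step 4.

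**1. Reproduce the stated figure.** Difference = 8853 − 6248 = 2605. Pooled SD = √((2030² + 3320²)/2) = 2752. Standardised difference d = 2605/2752 = 0.947. A two-sided two-sample t-test at 0.05 needs 19 per arm, or 38 in total, with power 0.810. A one-sided test would need only 15 per arm. The stated 38 is therefore exactly a two-sided comparison of post-intervention values.

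**2. Power of the planned test.** In a 2×2 mixed ANOVA the group-by-time F test equals the t-test on change scores. With equal pre and post SDs, SD of change = 2752 × √(2(1 − rho)). With 19 per arm:

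| rho | SD of change | Power | Evaluable total for 0.8 |
|---|---|---|---|
| 0.3 | 3256 | 0.67 | 52 |
| 0.4 | 3014 | 0.74 | 46 |
| 0.5 | 2752 | 0.81 | 38 |
| 0.6 | 2461 | 0.89 | 32 |

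A simulation with the article's unequal post-intervention SDs and a baseline SD of 2752 gave 0.66 at rho 0.3 and 0.80 at rho 0.5, so the unequal SDs hardly matter.

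**3. Break-even correlation by number analysed.** With 19 per arm, power is 0.80 when the SD of change is 2789. Then 2(1 − rho) = (2789/2752)² = 1.027, so rho = 0.49. A 20% loss from 46 leaves 46 × 0.8 = 36.8, about 18 per arm, and break-even is about 0.51. If all 23 per arm are analysed it is 0.37.

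**4. Break-even correlation by baseline SD.** Write S for the baseline SD and keep the two post-intervention SDs separate. The average variance of change is 2752² + S² − 2 × rho × 2675 × S, where 2675 = (2030 + 3320)/2. Setting this to 2789² with 19 per arm gives rho = 0.36 for S = 2030 and 0.61 for S = 3320. On this formula S = 2752 gives 0.50, close to the 0.49 in step 3.

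**5. The group main effect instead.** The effect halves to 2605/2 = 1302.5 and its SD is 2752 × √((1 + rho)/2). Power with 19 per arm is 0.42 at rho 0.3 and 0.34 at rho 0.7. Reading the test this way does not rescue the plan.

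**6. Baseline adjustment.** The residual SD is 2752 × √(1 − rho²). Ignoring the cost of estimating the slope, power with 19 per arm is 0.810, 0.845 and 0.906 at rho 0, 0.3 and 0.5. A simulation of ANCOVA with baseline as the only covariate (100,000 trials per rho, equal SDs), which includes that cost, gave 0.798, 0.834 and 0.898. Rounded, that is about 0.80, 0.84 and 0.90. The ratio of ANCOVA to change-score variance is (1 − rho²)/(2(1 − rho)) = (1 + rho)/2: 0.65 at rho 0.3, 0.80 at rho 0.6, and 1 only as rho reaches 1.

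**The case against.** The strongest reply is that no error in a number has been shown. The 38 reproduces, comparing change between randomised groups is a legitimate method, and the correlation that decides the matter is not in the article. If rho is above break-even, the planned test does better than 0.8. The break-even is not fixed either. Participants must report being physically inactive, so a baseline SD narrower than 2752 is plausible, though not documented, and would lower it. Analysing all 46 would lower it too. Finally, the tested term is inferred, because the article does not name the interaction.

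Most of this stands, and it limits the point. A reader might infer that the trial is underpowered. The documents do not support that, since they do not show on which side of break-even the trial lies. A reader might also infer that the ANOVA is invalid or biased. It is not: over randomisations the change comparison is unbiased and keeps its type I error.

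What does not stand is that the matter can be left to a later analysis plan. The article itself fixes both the basis of the sample size and the model, and the two do not match. Inferring the interaction is also safe, because the other candidate, the group main effect, has far lower power.

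**Conclusion.** The point holds as a mismatch between sizing and analysis. The stated 0.8 belongs to a two-sample test of post-intervention steps/day (actual power 0.81 with 38) and is not established for the planned group-by-time test. The size of the discrepancy is conditional. With 19 per arm and equal SDs, power runs from 0.67 at rho 0.3 to 0.89 at rho 0.6. Break-even lies between about 0.36 and 0.61 over the baseline SDs and numbers analysed that were tried. Confidence is high in the mismatch; no claim is made that power actually falls short.

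The planned test is valid but, except as rho nears 1, less efficient than adjusting for baseline. It would be too strong to say that adjustment guarantees 0.8 at every correlation: once the slope is estimated, power at rho 0 with 19 per arm is 0.798. Nor do the documents give any figure that would make a chance baseline imbalance likely, and the case for adjustment does not need one.

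**What to change.** State that the primary analysis of steps/day is the difference between groups immediately after the 12-week intervention, adjusted for baseline steps/day. This can be an ANCOVA, or a longitudinal model in which the two groups' baseline means are constrained to be equal. Name that adjusted difference as the test. It is the quantity on which the sample size was based, so the 38 evaluable then belong to the planned analysis.

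The cost is a change of wording and one model degree of freedom. The baseline accelerometer measurement is already scheduled, and no extra patients or data are needed.

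If the mixed ANOVA is kept, the sample size section should name group by time as the tested term, state the assumed pre-post correlation or SD of change with its source, and derive the number from that. Depending on the value, this could raise or lower the 38.
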